## Abstract

**Background:**

Pregnancy and motherhood increase the risk for long-term exposure to physical, psychological and sexual intimate partner violence (IPV; sexual or physical violence by current or former partners). Pregnant women and mothers with children under 5 who have experienced IPV exhibit poor physical and mental health and obstetric outcomes. Depression and posttraumatic stress disorder (PTSD) are the two most common mental health consequences of IPV. There is good evidence that women with good social support have better mental health and IPV outcomes.

**Methods:**

This study will develop MOthers’ AdvocateS In the Community (MOSAIC) Plus intervention for pregnant women and mothers with children under the age of 5. MOSAIC uses trained mentor mothers and has been found to reduce subsequent IPV. This study will blend the original MOSAIC intervention with principles of interpersonal psychotherapy (IPT) to address symptoms of depression, PTSD, and prevent subsequent risk of IPV. We will conduct a pilot randomized trial of the MOSAIC Plus intervention compared to the traditional MOSAIC intervention to determine its feasibility and acceptability. Study samples include focus groups (n = 36), open trial (n = 15), and a randomized pilot trial including 40 pregnant women and mothers with children under 5 who report current/recent of IPV and elevated symptoms of maternal depression and/or PTSD. The study’s primary outcome will be changes in maternal depressive and PTSD symptoms. Secondary outcomes will include reduction in subsequent IPV, improvement in functioning, changes in social support and effectiveness in obtaining resources.

**Discussion:**

This is a formative study evaluating the feasibility and acceptability of a mentor mother intervention for pregnant women and mothers with children under 5. Promising results of this study will be used for a larger, fully-powered randomized trial evaluating the effectiveness of a mentor mother intervention in preventing subsequent IPV and reducing depressive and PTSD symptoms in this population.

## Strengths and limitations of this study

The study is informed by a robust qualitative approach to intervention development that involves a series of focus group discussions.This study aims to develop an intervention that reduces future intimate partner violence, while also addressing related maternal mental health outcomes.A rigorous and reproducible design includes randomization, clear inclusion criteria, manualized treatment protocols and fidelity assessments.The study will use reliable and validated measures.Given the small sample size, results from the pilot randomized trial are underpowered to draw firm conclusions about effectiveness.

## 1. Background

Violence against women is a global human rights concern and a significant public health challenge; one in three women experience lifetime physical and/or sexual violence [1]. As many as 5.3 million U.S. women experience intimate partner violence (IPV; referring to sexual or physical violence by current or former partners) annually [2]. Depression and posttraumatic stress disorder (PTSD) are the two most common mental health consequences of IPV. In turn, developing depressive and PTSD symptoms after experiencing IPV increases future risk of IPV [3]. IPV is also associated with chronic physical health problems [4, 5] and self-harm [6].

Pregnancy and motherhood increase the risk for prolonged exposure to physical, psychological and sexual IPV [7]. IPV can start or worsen during the perinatal period. As many as 4% to 8% of women report IPV during pregnancy [8]. Compared to those who do not experience IPV, mothers who experience IPV during pregnancy or in the year following childbirth are at elevated risk for experiencing physical injury, other medical challenges, homicide [9] and mental health problems including suicide [10, 11]. Twenty percent of postpartum deaths are attributable to suicide [12].

Pregnant women and mothers who experience IPV may not seek care when they need it [13]. For example, perinatal women with experience of IPV may not initiate prenatal care until third trimester [14]. They are more likely than women without IPV to miss three or more prenatal visits [15]. Perinatal women with experience of IPV are twice as likely to have babies with low birthweight [16], higher rates of severe acute maternal morbidity [17] and have infants requiring intensive care [18]. IPV increases risk of depressive and PTSD symptoms, which in turn increases risk of subsequent IPV [8, 19–21].

Interventions are needed that address both, especially for pregnant women and mothers of young children [22–24]. There are very few interventions that effectively reduce IPV among pregnant women and mothers with children under 5 who report IPV [22–24]. One of them, Mother AdvocateS In the Community (MOSAIC) forms the basis of this study [25]. Very few existing interventions address maternal depressive and PTSD symptoms that often follow IPV [3, 26, 27]. An integrated intervention that addresses elevated symptoms of maternal depression and PTSD while reducing subsequent IPV is needed.

Mother AdvocateS In the Community (MOSAIC) [25] is a non-professional intervention delivered by mentor mothers from the community to reduce IPV in pregnant women and mothers with children under 5 [28]. The intervention combines elements of mentoring and IPV-specific support provided by mentor mothers. MOSAIC was tested in a fully-powered RCT for pregnant women and mothers with children under 5 in Australia and was found to reduce subsequent IPV [24]. However, the effects of the intervention depression were not significant and PTSD symptoms were not evaluated. The proposed study will augment MOSAIC with principles of an evidence-based intervention to improve maternal mental health. Interpersonal psychotherapy (IPT) is the front-line treatment for perinatal depression [29] and has been found to reduce PTSD symptoms in the perinatal period [30]. IPT addresses maternal mental health by helping women increase their general social support systems and build communication skills and confidence to access needed resources and help. IPT can be effectively delivered by lay providers [31]. IPT is theoretically consistent with the MOSAIC approach and addresses the consequences of IPV. IPT focuses on building or better utilizing one’s social support network within the context of a life stressor [32, 33]. The proposed study aims to integrate IPT principles into MOSAIC to address both IPV and its mental health sequelae.

Specifically, the study aims to:

Develop and pilot-test the feasibility and acceptability of MOSAIC Plus intervention in a sample of 40 women.Evaluate changes in symptoms of depression and PTSD.Assess reduction in subsequent IPV.Measure changes in functioning, self-care, general health and wellbeing, andEvaluate changes in social support and improvements in effectiveness obtaining resources.

## 2. Methods and analysis

### 2.1. Development phase

#### 2.1.1. Project advisory board

We will establish a project advisory board that will include 6–8 pregnant women and mothers with children under 5 and potential mentor mothers from the community. They will provide feedback on the content of the intervention in the development stage and on study procedures and results generally.

#### 2.1.2. Manual development

The goal of the development phase will be to develop the MOSAIC Plus intervention manual. We will begin with the MOSAIC intervention manual which was developed to reduce subsequent IPV experiences in perinatal women and mothers with children under 5 [28] but was not specifically designed to address concomitant mental health issues. The MOSAIC intervention uses non-professional befriending, domestic violence-specific advocacy and mentoring by mentor mothers from the community [34]. The mentor mothers may or may not have lived-experience with IPV, maternal depression or PTSD. MOSAIC Plus will expand the social support offered by mentor mothers in MOSAIC with IPT approaches for broadening women’s social support network generally. In MOSAIC Plus, we will expand the existing MOSAIC manual by integrating IPT approaches to address depressive and PTSD symptoms among IPV-exposed mothers. IPT conceptualizes interpersonal functioning and disturbance in social support as intimately linked to psychological symptoms [35]. IPT identifies a difficult life event or current interpersonal problem and addresses it by helping the individual to build or better utilize the individual’s extended social support network with specific IPT strategies that include psychoeducation, communication skills practice, and exploration/encouragement.

#### 2.1.3. Focus group discussions

We will conduct focus group discussions with potential study participants and potential mentor mothers to enhance and tailor the MOSAIC intervention to address mental health outcomes (reduction in depressive symptoms and PTSD symptoms). We will use information generated from focus group discussions to ensure that our manual expansion optimally addresses the needs of our target population, the mentor mothers, and the eventual implementing systems. We will conduct six focus group discussions of 6–8 members each (for 30–44 in total). Three groups with pregnant women and mothers of young children with current, recent or prior experience of IPV, 2 groups with potential mentor mothers, and one group with staff from community agencies (the settings where we would envision MOSAIC Plus being implemented if found promising). Focus group discussions will explore perspectives of potential clients and mentor mothers regarding the potential acceptability, benefits, and risks of the proposed MOSAIC Plus intervention and of the IPT components we plan to integrate. The goal of the 3 focus groups with pregnant women and mothers with children under 5 with IPV experiences will be to explore: (1) women’s perspectives on the greatest needs of IPV-exposed perinatal mothers; (2) what they would like most from mentor mothers to help with IPV, depression, and PTSD symptoms; and (3) feedback on the proposed MOSAIC Plus intervention and on the IPT-based components to be integrated. The goal of the two focus groups with nurse-family partnerships will be to explore ways to maximize acceptability of MOSAIC Plus, to integrate the intervention into their ongoing programs, and how to design the MOSAIC Plus program to maximize future implementability.

Participants for potential clients focus group discussions will be recruited from Hurley Medical Center’s perinatal clinic and YWCA using our standard study recruiting procedures and criteria. For the other two focus group discussions, we will recruit participants from local agencies serving mothers.

#### 2.1.4. Data analysis and manual development

A moderator accompanied by a note taker will facilitate the focus group discussions, which will be recorded by using a digital audio recorder. The recordings will be transcribed verbatim by an experienced transcriber. We will use the framework approach by using a framework drawn from the data. We will modify our coding framework based on the newly emerging themes. For rigorous and high-quality data management, we will use NVivo qualitative analysis software, version 12 [36]. We will develop an outline of the MOSAIC Plus intervention manual based on the original MOSAIC intervention manual. We will embed contents relevant to reducing depressive and PTSD symptoms to the new manual based on results of the focus group discussions. We will enhance, refine and adapt the MOSAIC Plus intervention for the outcomes of interest based on the results of the focus group discussions. [name] will conduct member checking with selected study participants to validate the fit, credibility and transferability of the results (i.e., main themes and translation of them into the manual itself) from the focus group discussions.

#### 2.1.5. Open trial

The second part of the development phase will include conducting a small open trial to further refine the intervention manual and assess feasibility of research procedures. We will recruit 15 pregnant women and mothers with children under 5 with experience of IPV, who also report elevated symptoms of depression and/or PTSD, meeting the same inclusion criteria as participants in the randomized trial (see sampling and recruitment section below), and who will receive the MOSAIC Plus intervention. We will review our strategies for recruitment and retention of participants, strategies for recruitment, supervision and retention of the mentor mothers and mentor mothers’ compliance with the study protocol. Participants will be requested to complete an intervention specific End-of-Treatment Questionnaire assessing perceived helpfulness of various components of the intervention and their comfort with the research processes and assessments. We will review the responses of participants at an exit interview to elicit information for further refining the intervention protocol.

#### 2.1.6. Program and procedure modifications

Based on data from the development phase, exit interviews, and ongoing feedback from the study team, the intervention manual, fidelity scales and the training program will be modified. Study recruitment and retention procedures will also be revised based on experiences of the research team and participants. These procedures will enhance study feasibility by ensuring that our assessments do not place undue burden on participants that measures are feasible and acceptable; and that dropout rates are minimized.

### 2.2. Pilot study phase

In the **pilot study phase**, the MOSAIC Plus intervention will be compared to the traditional MOSAIC in 40 women. The goal of this phase will be to assess the feasibility of the research design, the acceptability of the MOSIAC Plus intervention and to explore 95% confidence intervals of reduction around depressive and PTSD symptoms, and decrease in the experience of IPV within a 9-month period from intake. The duration of both interventions will be 9 months. Study assessments will take place at baseline, 3, 6 and 9 months.

#### 2.2.1. Sampling and recruitment

The randomized pilot study will involve 40 women who are 1) pregnant and/or are mothers of children under 5 and report IPV experiences in the past 6 months (as assessed by Composite Abuse Scale [37]) 2) aged 18 or above, and 3) have elevated depressive and/or PTSD symptoms (including full disorder). This will be determined using the Patient Health Questionnaire (PHQ-9) with a cutoff point of ≥9 [38], and the Davidson Trauma Scale (DTS) with a cut-off point of ≥40 [39]. We anticipate that the majority of study participants will have both elevated depressive and PTSD symptoms, given that 50% of individuals with PTSD also have comorbid major depressive disorders [40, 41], especially among women with IPV [21]. Participants will be excluded if they (1) cannot provide the name and contact information of at least two locator persons (~6%), and/or (2) do not have access to any telephone, (3) have a current serious mental illness requiring intensive care or (4) cannot understand English well enough to understand the consent form or assessment instruments when they are read aloud. Virtually all pregnant women and mothers of children under 5 accessing care in these settings speak English. An initial sample of 15 pregnant women and mothers with children under 5 will be recruited to participate in a nonrandomized open pilot trial and will receive the proposed MOSAIC Plus mentoring intervention. No woman will be excluded from recruitment on the basis of race, sexual orientation, gender identity? or disability status.

Participants will be recruited from two local agencies, the Hurley Medical Center OBGYN clinic and the YWCA-Flint. The YWCA offers domestic violence support, emergency shelter and long-term housing for persons with domestic violence exposure. For women identified as having a positive response to screening questions at those agencies, the provider in charge will ask “would you be interested in meeting with a person to hear about a voluntary project about peer support for pregnant women and mothers?”. The assessing provider will also explain that their decision whether to obtain additional information about the project has no potential impact on their access to other services at the agency. Women who are willing to meet with study staff will be given a referral slip by their providers which they will present to the study research assistant (RA). The study RA will meet potential participants in private locations at each agency. The RA will explain all aspects of the study, including confidentiality and its limits, and address questions. If the participant agrees, they will provide a written informed consent complete the baseline assessment. We will ask participants if they would like us to read consent forms aloud. The RA will emphasize that enrollment in the study is completely voluntary. Those who consent to participate will be provided with a copy of the informed consent document.

#### 2.2.2. The MOSAIC Plus intervention

The MOSAIC Plus intervention will be delivered to those in the intervention arm as specified in the manual, for the duration of 9 months. After completing the screening interviews, the study research assistant will introduce consenting, eligible participants to a MOSAIC Plus trained mentor mother (See training procedures below). The mentor mothers will work as a mentors and advocates in the areas of IPV safety planning, building social support, managing depressive symptoms and enhancing effectiveness obtaining community resources. During the initial phase, mentor mothers will explain their roles as a MOSAIC Plus intervention provider and exchange contact information (i.e., the participant’s contact information and the mentor mother’s study cellphone number). In the following four weeks, the MOSAIC Plus mentors will meet their clients in a private, confidential location to assess if there is ongoing IPV, conduct safety planning, strength and needs assessment. They will collaboratively set a realistic treatment plan for the intervention period. MOSAIC Plus mentor mothers will maintain regular contact with their clients at least once a week (may be more as needed). Information obtained during initial assessment (safety, strengths, needs) will be used to plan the rest of the mentoring intervention in the subsequent months.

After the initial phase is complete, as in the original MOSAIC intervention, mentor mothers will continue meeting their clients (in person or by phone) for a session no less than 60 minutes. This level of contact is high but was feasible and acceptable in the original MOSAIC trial [24]. In person meetings will take place in the community at convenient, private, and safe locations (libraries, treatment facilities, public buildings) as suggested by the clients. Telephone meetings will only be made from a study telephone line given to each mentor mother. The mentor mothers will review their clients’ activities since the initial planning meeting and problem-solve any challenges they may encounter. Mentor mothers also facilitate their clients’ access to other services by informing, educating and advocating for them when needed. Their services will involve 1) building social support networks by helping their clients solve any interpersonal difficulties they may have within their networks. Mentor mothers will also work with their clients by linking them with new social support groups and networks available in the community. They will focus on social support because strong social support protects against the negative effects of IPV on mental health [42]. 2) Mentor mothers will inform women about services and advocate for their access. Women with experience of IPV may have limited access to information, and hence poor access to services. Mentor mothers will help improve their access to services by actively identifying the needed services, creating proper linkage with providers and advocating for their access by addressing the barriers they may encounter. 3) Plan and monitor their safety by helping their clients create a personalized safety plan and monitor the potential of future violence and address any challenges they may have. Mentor mothers will employ the skills of active listening, reflecting and validating feelings, showing empathy, inspiring hope and facilitating a trusting relationship with other people in their personal networks or people who are service providers. The IPT component in this intervention includes the focus on addressing interpersonal conflict within the woman’s social network. MOSAIC Plus is consistent with the original intent of MOSAIC (support the mother directly), but utilizes a broader conceptualization (i.e., help the mother build her own social support network) and evidence-based IPT strategies for doing so.

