#### 2.2.3. The control condition

Those in the control condition will receive the MOSAIC intervention without the added IPT component. Participants in the control condition will also receive ongoing monitoring of depressive and PTSD symptoms and suicide ideation with appropriate referrals from mentor mothers. They will also be provided a county-specific IPV resource guide after consenting to enroll in the study.

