**MOSAIC Plus Feasibility and Acceptability (MOSAIC Plus participants only)**	
Acceptability (End of Treatment Questionnaire)	Endorsing an average score of 3 or more (out of 5) for each rated intervention component).
Quality of working relationship (WAI-SR)	Average > 36 (or a mean score of 3 or more [out of 5] on each of the 12 items). We will also descriptively examine goal, tasks, and bond subscales to see where mentor mothers are doing well and less well overall.
Satisfaction (Client Satisfaction Questionnaire-8)	Average > 24 (or a mean score of 3 on each of the 8 items)
Intervention attendance	70% of all participants complete at the initial session and at least 2 of 3 booster sessions
Intervention Fidelity	MOSAIC Plus intervention achieves at least 80% adherence on a random subset of sessions

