*2*.*2*.*8*.*2*. *Primary*: *Study Feasibility and Treatment Feasibility/Acceptability and safety*. We will assess feasibility of the research procedures by examining study recruitment and refusal rates, participants’ willingness to be randomized, follow-up rates, reliability and range of responses to study questionnaires. We will assess the feasibility and acceptability of MOSAIC Plus by examining treatment completion (based on the jointly established treatment plan) and drop-out. We will examine reasons for termination from study and/or intervention for consistent patterns. We will examine the acceptability of the MOSAIC Plus intervention by using data from CTQ-8 treatment satisfaction questionnaire, the End of Treatment Questionnaire, and detailed exit interviews. Clients’ experiences with the mentor mothers, the quality of their working relationship and their level of satisfaction with the service will be evaluated using the Working Alliance Inventory-Short Revised (WAI-SR). Moreover, as in the original MOSAIC study [34], we will also explore perspectives of the mentor mothers regarding acceptability of the MOSAIC Plus intervention. We will use Competency Assessment Inventory (CAI), which tests the attitudes, knowledge, and skills needed to provide high-quality mental health care (i.e., learns and respects clients’ preferences about intervention, creates opportunities for clients to practice skills).

At the end of the open trial and at 2 time-points during the RCT (i.e., after enrolling 20 and 40 participants), we will compute the descriptive data on all target outcomes described in Table 2. The scientific team will convene to discuss how our actual outcomes compare to target outcomes. If the team identifies discrepancies between target outcomes and actual outcomes, we will 1) investigate the reason for failure to meet the stated outcomes, and 2) discuss among the research team. Depending on the nature of the discrepancy, we may modify recruitment or assessment procedures, instructions to participants, training procedures, or other trial aspects. Table 1 below presents assessment methods.

**Table 2 pone.0267679.t002:** Target mechanisms.

Target Mechanism 1: Social support	
Definition	“Emotional, informational and practical assistance provided in a supportive social network” [69]
Evidence that adding IPT approaches increase social support	IPT has been found in many studies to increase social support relative to control conditions [70–73]

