*2*.*2*.*10*.*4*. *Target mechanisms*. We will separately calculate the effect size and 95% CI for the effect of the intervention on proposed target mechanisms including improved social support (measured using MOS-SS) and effectiveness obtaining resources (measured using EOR scale). Separate exploratory tests for differences between conditions will use HLM, with baseline scores as covariates. We will then explore the association of each of these target mechanisms with changes in our primary outcome (reduction in depressive and PTSD symptoms) from baseline through 9 months. These exploratory analyses will inform full tests of mediation (i.e., tests of the hypothesis that the effects of MOSAIC Plus on reduced depressive symptoms is mediated through improvement in social support and effectiveness obtaining resources) in a subsequent fully powered trial. Although we expect the MOSAIC Plus intervention show evidence of preliminary effectiveness, should the intervention show no or limited evidence, exploratory tests of target mechanisms will also provide some initial information about whether MOSAIC Plus’ limited effectiveness was due to failure to engage target mechanisms or to the target mechanisms not being associated with the final outcome. Target mechanisms are presented in Table 2 below.

*2*.*2*.*10*.*5*. *Personalization and processes*. We will explore marital status, maternal age, race/ethnicity, household income, parity, severity of IPV experience, gestational age at enrollment, and number of lifetime trauma experiences (as assessed by the Trauma History Questionnaire) [83] as predictors and moderators of treatment outcome. These variables were also used in the original MOSAIC study [24] and other studies with women with IPV experiences [25, 46, 84]. We expect that MOSAIC Plus will be appropriate for a full range of perinatal women with IPV experience. Preliminary analyses of dose-response effects will also be conducted.

*2*.*2*.*10*.*6*. *Treatment Integrity*. We will calculate scale reliabilities of adherence and competence ratings using both individual item correlations and total intraclass correlations. We will compute scale validity by correlating adherence and competence ratings to intervention outcomes, to each other, and to expert ([name]) ratings. Adherence and competence ratings of trained raters will be compared to expert global ratings to determine cut-off scores with sufficient sensitivity and specificity.

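### Extra contact follows need and its targets cover one arm only, so a dose-response analysis on total contact would be open to confounding and the stated metrics do not check contact balance between arms

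*Protocol article*

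**What the plan says.** On delivery, section 2.2.2 states: "MOSAIC Plus mentor mothers will maintain regular contact with their clients at least once a week (may be more as needed"). It adds: "Information obtained during initial assessment (safety, strengths, needs) will be used to plan the rest of the mentoring intervention in the subsequent months". Contact above the minimum therefore depends on the woman's need, and no upper limit is given.

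On analysis, section 2.2.10.5 says only: "Preliminary analyses of dose-response effects will also be conducted". It gives neither a definition of dose nor an adjustment set. The exploratory models elsewhere in section 2.2.10 use the baseline score as covariate.

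On measurement, the block of Table 1 that holds attendance, the WAI-SR, the Client Satisfaction Questionnaire-8 and fidelity is headed "MOSAIC Plus Feasibility and Acceptability (MOSAIC Plus participants only"). Section 2.2.8.2 is framed the same way: "We will assess the feasibility and acceptability of MOSAIC Plus by examining treatment completion (based on the jointly established treatment plan) and drop-out".

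On the comparator, section 2.2.3 says: "Those in the control condition will receive the MOSAIC intervention without the added IPT component". It states no contact frequency or session length for that arm. Section 2.2 gives both interventions a duration of 9 months.

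**The concern.** There are two separate issues.

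The first is confounding by need. If a woman whose symptoms or violence worsen in month 4 is seen more often because of it, her contact total rises and her later score is worse for the same reason. A regression of outcome on total contact then partly measures need. The baseline score cannot absorb this, because the need arises after baseline. A real benefit of contact could be masked or could appear as harm.

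The second is attribution. The control is meant to be the same mentoring without IPT, and the Discussion says the pilot prepares a fully powered trial of the same comparison. With contact open-ended, equal exposure in the two arms is an assumption. The stated targets examine attendance and completion in MOSAIC Plus alone, so they would not show whether that assumption held. The next trial would then be planned on a difference whose source is unclear.

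**Working it through.** **1. What the plan fixes.** It gives no figure for dose, so there is none to reproduce. If the weekly rule runs for the full 9 months, the floor is 9 × 52/12 = 39 contacts. The attendance target in Table 1 counts the initial session plus 2 of 3 boosters, that is 3 of 4 sessions. These are two different scales of dose in one document. It is also unclear whether the weekly rule extends beyond the four-week initial phase.

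**2. Bias when contact tracks severity.** All inputs here are assumptions. Let U be current severity, with correlation ρ with baseline. Dose is D = gU + √(1 − g²)·e, so g is the correlation of dose with current severity. Outcome is Y = 0.6U − 0.20D + noise, so the true dose effect is a benefit of 0.20 SD per SD of dose.

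- Unadjusted slope = −0.20 + 0.6g
- Baseline-adjusted slope = −0.20 + 0.6 × g(1 − ρ²)/(1 − g²ρ²)

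| g | Unadjusted | Adjusted, ρ = 1 | Adjusted, ρ = 0.6 |
|---|---|---|---|
| 0 | −0.20 | −0.20 | −0.20 |
| 0.3 | −0.02 | −0.20 | −0.08 |
| 0.5 | +0.10 | −0.20 | +0.01 |

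For example, with g = 0.3 and ρ = 0.6: 0.3 × 0.64/(1 − 0.09 × 0.36) = 0.192/0.9676 = 0.198, and −0.20 + 0.6 × 0.198 = −0.08. Baseline adjustment works only if need is fully captured at baseline (ρ = 1). If g = 0 there is no bias.

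**3. The same point with no true effect.** This simulation of 200,000 women also rests on assumed inputs: monthly severity autocorrelation 0.85; 39 planned weekly contacts, each kept with a woman-level probability drawn from Beta(8,2); on average 0.3 extra contacts a week, rising by a factor exp(b) per SD of severity. The baseline-adjusted correlation of total contacts with the 9-month score, for b = 0.25, 0.5 and 0.75, was +0.21, +0.36 and +0.44 (more contact, worse outcome). With the outcome taken one month after the last severity update it was +0.16, +0.29 and +0.36. At b = 0 it was 0.00.

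**4. Would another dose measure cure it?** The share of planned weeks with at least one contact, capped at one a week, gave 0.00. That result follows from simulating attendance as independent of severity. In a run where attendance did depend on severity, the capped measure showed −0.18, a spurious benefit. Adjusting for a score taken after the counted dose is also unsafe: in another run it shrank a true effect from about −0.11 to −0.03, because that score already carries part of the dose effect.

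**5. Arm contrast.** The part of a symptom difference due to contact is the slope times the gap in contact. At an assumed slope of 0.20:

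- gap 0: 0.20 × 0 = 0
- gap 0.5 SD: 0.20 × 0.5 = 0.1 SD
- gap 1 SD: 0.20 × 1 = 0.2 SD

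The 95% CI half-width for d at 20 per arm is 1.96 × √(2/20) = 0.62. At 14 per arm (70% of 20, the 6-month retention target) it is 1.96 × √(2/14) = 0.74.

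**The case against.** A reader might infer that the arm contrast is compromised because MOSAIC Plus women receive extra contact. The document does not support that. After the initial phase, "as in the original MOSAIC intervention, mentor mothers will continue meeting their clients", and of the intensity it says: "This level of contact is high but was feasible and acceptable in the original MOSAIC trial". Both arms last 9 months and the control is MOSAIC without IPT. Nothing assigns more contact to MOSAIC Plus, and even if contact diverged, randomisation would still protect the estimate of the package effect. This objection stands in full.

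A reader might also infer that the planned dose-response analysis is already confounded. That too goes further than the text allows. The dose is undefined, its definition may sit in an analysis plan that is not shown, and section 2.2.8.2 hints at another measure, completion of the jointly agreed plan. What can be said is conditional: an analysis on total contact would be exposed. The delivery rule that creates the exposure is fixed in this document, and contact that is not logged during delivery cannot be recovered by a later analysis plan.

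Targets are not the same as data collection. The heading in Table 1 limits benchmarks and does not say that control data go uncollected. Section 2.2.7 has adherence checklists for each meeting in both conditions. Section 2.2.8.2 describes the WAI-SR without limiting it to one arm, and section 2.2.9.5 has mentors rate the alliance with each participant. Part of the fix may therefore already be intended, but no stated metric compares contact between arms.

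Finally, the stakes are modest. The analysis is called preliminary, the article says the pilot is underpowered for firm conclusions, and its primary goal is feasibility. At n = 20 with one covariate, the Fisher-z 95% interval is about −0.11 to 0.70 for a correlation of 0.36 and −0.02 to 0.75 for 0.44, so even the larger one includes zero. This stands as a limit on the harm. It also means that a dose-response result from this pilot would be both imprecise and open to bias.

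**Conclusion.** The concern holds in a limited form. Because contact above the weekly minimum follows need, a dose-response analysis on total contacts or hours would be open to confounding by need arising after baseline, which baseline adjustment does not remove. The size and direction depend on how far contact tracks severity. Under the assumed inputs the bias runs from nothing to enough to cancel a true benefit of 0.20 SD.

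Separately, the stated metrics do not check equality of contact between arms. The randomised contrast remains a valid estimate of the package effect, but a difference could not be attributed to IPT rather than to contact. In this pilot a contact-driven part of 0.1 to 0.2 SD would be small against a CI half-width of 0.62, so the value of the check lies mainly in designing the larger trial. The mismatch between the attendance target and the weekly contact rule is a plain inconsistency and rests on no assumption about severity.

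**What to change.** **Table 1 and section 2.2.8.2.** Log the date, mode and minutes of every mentor contact in both arms. Apply the attendance measure, the WAI-SR and the Client Satisfaction Questionnaire-8 to both arms, or state that this is already intended. Report contact by arm beside the effect sizes.

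**Section 2.2.10.5.** Label the dose-response analysis descriptive. Do not use total as-needed contacts as the dose. Use the share of planned weeks with a contact as the main measure and show as-needed extras separately. Adjust only for scores measured before the dose interval. State that residual confounding remains if attendance depends on severity.

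**Table 1 and section 2.2.2.** Reconcile the attendance target (initial session and 2 of 3 boosters) with the contact of at least once a week, so that dose has one meaning.

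**Cost.** Contact-log entries by mentors, two short questionnaires for about 20 control women, and revised wording. The burden is slight, and contact above the minimum can still follow need.
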